#### Primary outcome

A change in muscle CSA is a direct reflection of the intervention’s ability to restore muscle protein and a direct consequence of the net protein balance over time in the target muscles. We chose m. quadriceps and m. vastus lateralis CSA based on MRI scans of the dominant thigh as the primary outcome, as it directly reflects the intervention’s ability to counteract age-related loss of muscle mass. MRI scans have high sensitivity and validity in terms of lean mass in skeletal muscle [61], and previous researchers have considered this modality superior to DXA [62, 63].

Each scan consists of six axial slices, with the first slice placed in the medial tibia plateau. Each slide is 8 mm thick and separated by a 60-mm gap as shown in Fig. 4. The primary time interval for assessment is from baseline to 12 months.

**Fig. 4 Fig4:**
[figure not shown]
Magnetic resonance imaging analysis. We place slices as shown for analysis of cross-sectional area of the m. quadriceps femoris muscle and analyze slices 3 (counting in distal to proximal direction) and 4 for all subjects, and we use slice 4 for primary outcome evaluation. We fix the placement of slices in absolute distances, but we measure the femur length on dual-energy X-ray absorptiometric scans from the lateral tibial plateau (0 %) to the top of the greater trochanter (100 %) to report the relative placement of slices. Currently, placement of slice 3 ranges from 27 % to 36 % and slice 4 from 40 % to 54 % of the femoral length, depending on the height of the participant

#### Secondary outcomes

##### Thigh isometric peak torque

After having the participant perform a brief warm-up on a cycle ergometer, a tester will measure the dominant thigh peak strength at 70-degree flexion (0 degrees represents horizontal) in a Kinetic Communicator (model 500-11, Kinetic Communicator; Isokinetic International, Chattanooga, TN, USA) with verbal encouragement. An investigator will choose the best of three sweeps (i.e., highest peak force) for analysis. The rate of force development and impulse will also be analyzed [51, 64].

##### Thigh isokinetic peak torque

Using the same settings as those used for the isometric peak strength exercise, the same tester will measure the dominant thigh isokinetic (at 60 degrees/second) force. With verbal encouragement, participants will perform maximal sweeps until peak values decline markedly from the best sweep on that particular test day, and the test is finished. An investigator will choose the best sweep (i.e., highest peak torque) and analyze the peak torque, total work, and angle at peak torque [51, 64].

##### Power rig

After recording the isometric and isokinetic peak torques, the tester will measure the maximum single-leg extensor power of the dominant leg using a University of Nottingham leg extensor power rig according to procedures described elsewhere [65]. This test is known to correlate with physical performance [8] even more than muscle strength [66] and serves to link the changes in strength to functional outcomes. During the test, participants are in a seated position, and a single maximum explosive leg extension accelerates a flywheel from rest. A computer calculates the power of the leg extensors on the basis of the speed of the flywheel. The participants familiarize themselves with the procedure by performing two warm-up trials followed by a minimum of five and a maximum of ten maximal trials with approximately 30 seconds of rest between them.

##### 30-second chair-stand

The 30-second chair-stand test is a functional assessment of strength and endurance in the lower extremity by measuring the number of stands completed in 30 seconds with hands crossed on the chest [67]. The test is useful in characterizing the participant’s functionality and is also known to correlate with daily activity level [68].

##### Muscle biopsies and fiber-type composition

Working in sterile conditions, a qualified researcher will obtain muscle biopsies from the dominant m. vastus lateralis *ad modum* Bergström [69] with suction using the local anesthetic lidocaine 1 %. One biopsy is taken before and one after 12 months of the intervention, approximately 2–3 cm apart in a proximal-to-distal direction.

##### Body composition

A trained operator will perform whole-body DXA using the enCORE v.16 software (Lunar iDXA; GE Medical Systems, Pewaukee, WI, USA). Participants arrive having refrained from solid foods from 21:00 the day before the baseline and 12-month scans, and we perform scanning between 08:00 and 10:00. We obtain the remaining scans in the fed state at all times of the day, but prior to all scans participants are euhydrated and instructed to void. Whole-body composition is autoanalyzed, and, on a separate occasion, a blinded investigator performs separate thigh analyses manually with a region of interest (ROI) defined proximally by drawing a horizontal line laterally from the distal part of the groin and distally by drawing a line horizontally through the medial tibial plateau [70–72]. The thigh ROIs are equal in size in each subject but vary with thigh length between subjects.

##### Bone mineral density

In the same baseline and 12-month DXA sessions, the same operator scans the bone mineral density in the lumbar region (L2–L4) and the dominant collum femoris. The investigator will place the vertebral ROI as caudal as possible, including the discus caudal to the vertebra, making sure not to include the adjacent vertebra or spinous process. On the collum femoris scan, the investigator places the ROI as distal as possible without including the greater trochanter [73, 74].

##### Gut microbiome

At 0, 6, and 12 months, participants place a fecal sample in an insulated bag with freezer elements until delivery at Bispebjerg Hospital within 48 h. The container is then stored at −60 °C until further analysis. Following homogenization, we extract the total DNA using the PowerSoil DNA isolation kit (MO BIO Laboratories, Carlsbad, CA, USA) with an initial bead-beating step and employ tag-encoded *16S* ribosomal RNA gene (prokaryotes) and internal transcribed spacer region (eukaryotes) high-throughput sequencing using the MiSeq platform (Illumina, San Diego, CA, USA) to characterize the prokaryotic and eukaryotic components of the gut microbiome. As previously reported [75], we purify, extract, and sequence the virus-like particles for characterization of the gut virome.

##### Fecal metabolome

We will analyze the fecal metabolite extracts by performing gas chromatography with time-of-flight mass spectrometry (GC-TOF-MS) and nuclear magnetic resonance (NMR) spectroscopy using the same metabolite extract. The extraction procedure will involve stabilization of the homogenized fecal samples in PBS (pH 7.4) followed by freeze-drying and subsequent resuspension in methanol. We will perform untargeted metabolomics analysis and targeted profiling of short-chain fatty acids with a high-throughput GC-TOF-MS setup consisting of an Agilent 7890B gas chromatograph (Agilent Technologies, Santa Clara, CA, USA) and a high-throughput Pegasus TOF-MS spectrophotometer (LECO, St. Joseph, MI, USA). To increase GC-TOF-MS sensitivity toward a broad spectrum of nonvolatile metabolites, we will derivatize the samples as previously described [76] followed by processing of the obtained complex raw data using state-of-the-art three-way decomposition methods with Parallel Factor Analysis 2 [77]. We will further stabilize the fecal metabolite extracts using PBS prior to performing one-dimensional ^1^H NMR measurements using an AVANCE III 600 spectrometer (Bruker BioSpin GmbH, Rheinstetten, Germany) operating at a Larmor frequency of 600.13 MHz for protons and equipped with a cooled high-capacity autosampler (SampleJet; Bruker BioSpin GmbH) [78].

##### Plasma metabolome

We will collect the plasma samples with participants in fasting condition prior to the oral glucose tolerance test (OGTT) at 0 and 12 months and in fed condition at 6 and 18 months. Researchers will draw the blood into two containers, one containing tripotassium ethylenediaminetetraacetic acid (K_3_-EDTA) and one with heparin, and, after centrifugation at 3970 rpm for 10 minutes at 4 °C, we will pipette plasma into vials that are stored at −60 °C. We then will perform untargeted metabolomics of all samples using proton one-dimensional ^1^H NMR spectroscopy and for a subset of the samples by GC-TOF-MS.

We will perform the NMR measurements according to standard operating procedures developed for NMR metabolomics of plasma samples [79], and the data will provide unbiased metabolic fingerprints of the plasma samples, including information about lipoprotein particle distribution [80]. Prior to GC-TOF-MS analysis, we will thaw, vortex, and centrifuge the plasma samples at room temperature followed by addition of ice-cold acetonitrile in 1:3 (vol:vol) to precipitate proteins. Immediately after this, we will vortex the samples vigorously and centrifuge them at 20,000 × *g* for 10 minutes at 4 °C, and we will then dry 50 μl of clear supernatant under reduced pressure, derivatize it as described previously [76], and subject it to GC-TOF-MS.

##### Muscle protein synthesis

To assess MPS, we will perform an 8.5-h primed, continuous infusion of a stable isotope-labeled amino acid tracer, L-[ring-^13^C_6_]phenylalanine (Cambridge Isotope Laboratories, Tewksbury, MA, USA) at baseline and after 12 months of the intervention in a random subset of participants from each of the five intervention groups. The participants will fast overnight fast, and we will start the tracer infusion followed by collection of muscle biopsies after 1.5-h and 4.5-h infusions to measure the basal resting MPS over a 3-h period. Thereafter, we provide a protein drink as a beverage containing 20 g of whey hydrolysate plus 10 g of maltodextrin followed by collection of the third muscle biopsy. After an additional 4 h, we will measure the postprandial response of MPS. We will sample the muscle biopsies from the m. vastus lateralis muscle approximately 3 cm apart in a proximal-to-distal direction. Throughout the day, we will collect venous blood samples to measure tracer enrichment as well as amino acid and insulin concentrations, and we will measure the enrichment of phenylalanine tracer in blood and free in muscle cells by GC-MS/MS, whereas we will measure the incorporation of labeled phenylalanine in muscle proteins using GC-combustion/isotope ratio MS. We will then calculate the fractional synthesis rate (FSR) as the difference of incorporated tracer between subsequent biopsies (E_p2_ − E_p1_) divided by the precursor enrichment (E_precursor_; venous plasma and muscle free enrichment) and divided by incorporation time: FSR (%/h) = [(E_p2_ − E_p1_) × (E_precursor_)^−1^ × (incorporation time)^−1^] × 100 % [81]. This setup allows the evaluation of both basal MPS and the MPS response to a protein/carbohydrate drink before and after the 12-month intervention as a measure of muscle anabolic responsiveness to intake of a single protein supplement. We will also analyze muscle biopsies for relevant myocellular gene expression using real-time reverse transcriptase-polymerase chain reaction and for protein signaling through, for example, mammalian/mechanistic target of rapamycin complex 1 by performing Western blotting.

#### Tertiary outcomes

##### Blood parameters and anthropometry

At baseline, we will obtain standard health screening blood samples. At the remaining time points, we will measure only plasma HbA1c, cholesterol, and creatinine. Moreover, we will measure body weight, waist, and hip circumference at the remaining time points, whereas we will measure only height at baseline. Participants will wear underwear only when we measure body weight at baseline and 12 months, and they will wear light clothing at 6 and 18 months.

##### Hand grip strength

We will evaluate hand grip strength of the dominant hand (bilateral testing at baseline) by using a hand grip strength dynamometer (DHD-1 [SH1001]; SAEHAN Corporation, Changwon City, South Korea). The tester allows at least 30 seconds of rest between a minimum of three attempts, and the highest value at the given time point is used. The test is finished when two consecutive measurements are lower than the peak value [82].

##### 400-m walk test (fast gait speed)

On a 20-m course marked with two colored cones, the physical examiner instructs the subject to walk 400 m as fast as possible without personal support or sitting down. Up to 1 minute of standing is permitted if the participant feels tired or experiences discomfort, as long as the test is completed within 15 minutes [83]. Among several functional measures, we chose 400-m gait speed as it is one of the more demanding functional tests available for elderly populations. This minimizes the risk of a ceiling effect among the included participants whom we expected to be relatively well-functioning.

##### Health-related questionnaires

At baseline and 12 months, we will hand out Danish translations of the 36-item Short Form Health Survey [84] and the Pittsburgh Sleep Quality Index [85], which the subjects complete without further instructions.

##### Activity monitoring

We measure 4-day (96-h) overall activity by mounting an activity monitor (activPal 3™, activPal 3c™, or activPal micro; PAL Technologies, Glasgow, UK) on the anterior surface of the thigh. The period always covers an entire weekend. An investigator will analyze data quantified as step counts, time in sitting/lying position, time in standing position, and time walking [86, 87].

##### Weighed food registration

We will administer a 3-day weighed food and liquid registration from Wednesday to Friday before, 4–6 weeks after, and 50 weeks after commencing the intervention. Investigators subsequently will quantify total daily intake and meal distribution of macronutrients using the MADLOG VITA system (MADLOG ApS, Kolding, Denmark).

##### Sensory and hedonic evaluation questionnaires

Participants will complete a questionnaire about their experience with taking the dietary supplements. We will collect baseline data on the first consumption day (day 0) and weekly for 12 weeks. Thereafter, we will reevaluate participants every third month until week 52. The flavor of the supplements will be alternated every week between fruit and cacao, and the participants will fill in the questionnaires within 1 minute after ingestion of the supplement. We will measure the participants’ acceptance after the first sip and after complete consumption on a 9-point hedonic scale ranging from 1 = “do not like at all” to 9 = “like a lot,” with neutral in the middle. After the first sip, we will record the participants’ perceived experiences using the check-all-that-apply method with 20 attributes of taste, flavor, mouth feel, and sensory appeal of the dietary supplement. After participants consume the supplements, we will collect data on how satiating, refreshing, and easy to drink it was, as well as on the strength and persistence of the aftertaste on a 9-point scale ranging from 1 = “completely disagree” to 9 = “completely agree,” with neutral in the middle.

##### Satisfaction with Food-related Life scale

Subjects will complete the Satisfaction with Food-related Life scale [88] on days 0, 90, 180, and 360 to identify factors contributing to satisfaction with food-related lifestyle.

##### Oral glucose tolerance test

Participants will undergo two OGTTs during the study. Participants will fast overnight, and a researcher will draw a basal venous blood sample and then administer 75 g of anhydrous glucose dissolved in 250 ml of tap water. Subsequently, the researcher will draw blood at 45 and 120 minutes after consumption of the glucose. Participants will lie supine throughout the 2-h period [89]. We will draw blood in K_3_-EDTA vials and cool the vials for at least 15 minutes, centrifuge the sample for 10 minutes at 3970 rpm at 4 °C, immediately analyze the plasma for glucose, and store aliquots at −80 °C for subsequent insulin measurement. At baseline, we draw two further blood samples in K_3_-EDTA and heparin vials respectively, which are cooled on ice, centrifuged for 10 minutes at 3172 × *g*, and the plasma is then stored at −60 °C until metabolome analysis.

#### Qualitative interviews and observations

##### Qualitative interviews

Upon participant inclusion, a researcher will conduct a short, standardized, qualitative interview with the participant to gain information on marital status, living conditions, work life, hobbies, and dietary preferences. At the 18-month follow-up, a researcher will interview the participants to gain information about their experience with the intervention and current habits regarding nutrition and exercise.

##### Questionnaire on food habits

At baseline, the staff will hand out a questionnaire with a range of questions about the food perceptions and habits of the participant. The questionnaire combines basic socioeducational data, quantitative questions, and quantifiable qualitative questions about lifestyle changes, dietary changes and perceptions, and intake of protein-rich foods. The participants can complete the questionnaires during the first 3 months and subsequently hand them in.

##### Life story interviews

We will select 25 of the intervention participants for 1.5- to 2.5-h life story/trajectory interviews in their own homes. The main themes of the interviews are past and present perceptions of and habits concerning food and physical activity, but we will also include questions regarding mobility and work life.

##### Ethnographic fieldwork

We will select 48 research participants to engage in a qualitative study focused on everyday life routines, eating practices, physical activity, and experiences with participating in the trial. We do this by observing the research participants in their homes and at the site of the clinical trial, thereby following their daily activities in both settings. Further, we will conduct semistructured qualitative interviews to gain in-depth knowledge about selected individuals.

### Data collection, management, and analysis

According to Danish research ethics legislation, we will inform the participants about their rights as voluntary subjects in a scientific trial and interview them about their motivation for participation. We do this to make participants consider participation thoroughly to diminish the likelihood of their dropping out. We are obliged to report any unforeseen adverse effects due to participation to the local ethical committee, which will consider terminating the project depending on the reported incidents.

We will collect and manage study data using REDCap electronic data capture tools hosted at RegionH (Copenhagen, Denmark) [90] and secure it according to Danish Data Protection Agency legislation (approval on 9 January 2015, number 2012-58-0004 – BBH-2015-001 I-Suite 03432). This includes pseudoanonymization of sensitive data. Only relevant staff have logged access to the key file.

The project has a scientific advisory board with experts from all scientific disciplines applied in the research, and its members meet annually with the researchers to discuss progress and plan future work. The board members are financially and personally unrelated to the study investigators and the project as such.

The principal investigators from each scientific discipline have a shared responsibility to secure and monitor data collection and interpretation, and thus they are all involved in project management, analysis of samples, data collection, and observations and will all have access to the final dataset and jointly be involved in the interpretation of results.

### Statistics and power calculations

For all power calculations, we will apply a level of significance of 0.05 and a power of 0.80, and the primary outcome is the degree of muscle hypertrophy determined as the change in quadriceps muscle CSA on MRI scans over the course of the 12-month intervention. On the basis of previous data [91], we set the following parameters: least average expected change over the course of the 12-month intervention between distinct intervention groups, 300 mm^2^ (corresponding to an estimated relative change of 6.5 %) with a SD set to 140 mm^2^. Our goal is to be able to detect differences between groups’ mean hypertrophy down to approximately 2 %, which corresponds to approximately 80 mm^2^. A difference in the change of quadriceps muscle CSA greater than 80 mm^2^ between any two groups is statistically detectable with a power of at least 0.80 with a group size of 30. We decided to include 35 subjects in each of the three groups (HRTW, LITW, and CARB), as we anticipated a dropout rate of 15 % at the time of study initiation. In the WHEY and COLL groups, we expected a larger dropout rate because of taste issues with protein supplements and no motivational effect by training as in the HRTW and LITW groups. Thus, we will include 50 each in the WHEY and COLL groups. On an ad hoc basis, we will evaluate the actual dropout rate and adjust the total number of inclusions accordingly.

In a subset of participants from the five intervention groups, we will conduct experimental tracer studies before and after the 12-month intervention period to determine the extent to which the interventions affect the responsiveness of MPS to protein intake. The goal is to measure whether any of the interventions enhance the anabolic sensitivity to protein intake and thereby investigate if we can link the observed differences in muscle mass over the course of the intervention period to changes in the anabolic response to protein feeding. Thus, the outcome measure is the relative change in the FSR of muscle proteins from the basal condition, defined as the overnight fasted and resting state, to the average 4-h postprandial period after intake of a standard protein bolus. We are not aware of any data on changes in MPS responsiveness over time, and we therefore based the power calculations on a sum of our own published and unpublished data obtained in healthy elderly participants. We established the following parameters: expected average 4-h postprandial responsiveness to protein feeding from basal condition of 0.016 %/h (i.e., approximately corresponding to an increase in muscle protein FSR of 50 %) with an interparticipant SD on the increase of 0.017 %/h. We aim to be able to detect a 50 % change in responsiveness within a group over the course of the 12-month period (i.e., a change of 0.008 %/h in the increase in the muscle protein FSR from 0.016 %/h to 0.024 %/h). The SD for the change in responsiveness is set as 0.006 %/h. By including 10–12 participants, we obtain a power of at least 0.80 to detect a statistical difference over time within each intervention group. By taking the probability of dropouts into account, we decided to include 12 participants in the HRTW, LITW, and CARB groups and 15 in the WHEY and COLL groups, respectively.

Investigators will analyze data as intention-to-treat (except in subgroup analyses) as well as per protocol, and we will test the following groups against each other using one-way analysis of variance of the relative group changes from baseline to 12 months: (1) WHEY vs. COLL vs. CARB and (2) HRTW vs. LITW vs. WHEY. We will not conduct any interim analyses in this project.

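### With the protocol's own SD of 140 mm², 30 per group gives power of about 0.59, not at least 0.80, for an 80 mm² difference between two groups

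*Protocol article*

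**What the plan says.** All inputs stand in one paragraph of the protocol article, section Statistics and power calculations.

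- Error rates: "we will apply a level of significance of 0.05 and a power of 0.80". Sidedness is not given.
- Expected effect and variability: "least average expected change over the course of the 12-month intervention between distinct intervention groups, 300 mm^2", equated with 6.5 %, "with a SD set to 140 mm^2". This is the only SD given for the primary outcome.
- Goal: to detect differences in mean hypertrophy of roughly 2 %, "which corresponds to approximately 80 mm^2".
- Claim, made for every pair of groups and any gap in CSA change above 80 mm²: "statistically detectable with a power of at least 0.80 with a group size of 30".
- Enrolment: "We decided to include 35 subjects in each of the three groups (HRTW, LITW, and CARB), as we anticipated a dropout rate of 15" per cent. WHEY and COLL get 50 each because more dropout was expected there.

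The end of the same section plans a one-way ANOVA of relative changes from baseline to 12 months in two sets of three groups: WHEY, COLL and CARB; and HRTW, LITW and WHEY. No covariate adjustment or other variance reduction is mentioned.

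**The concern.** The goal of 80 mm² is only 0.57 of the stated SD. A standardised difference of that size normally needs about 50 per group, so a claim of 0.80 power at 30 per group looks wrong on sight.

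This paragraph is the only sample-size justification for the primary outcome, and the enrolment of 35 in three groups follows from the 30 completers. The comparison of HRTW with LITW is the most exposed. Both are 35-person groups, and the second working hypothesis predicts a similar or better response to light training under intention to treat. A non-significant result there could easily be taken as similarity, and a citation of 80 % power for a 2 % difference would lend that reading support it does not have.

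**Working it through.** **Inputs** (all from Statistics and power calculations): Δ = 80 mm², SD = 140 mm², n = 30 per group, alpha = 0.05. Two-sided testing is assumed; one-sided is also shown.

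**1. Attempt to reproduce the stated power.**
- Standardised difference: d = 80/140 = 0.571.
- Standard error of the difference: 140 × √(2/30) = 36.15 mm².
- Noncentrality: 80/36.15 = 2.21, with 58 degrees of freedom and critical t = 2.00.
- Power from the noncentral t distribution: **0.586** (0.600 by the normal approximation). One-sided: 0.706.

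The stated value of at least 0.80 is not reproduced.

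**2. What 0.80 would require.**
- n per group = 2 × (1.960 + 0.842)² × (140/80)² = 48.1, so 49 by the normal approximation. By the exact t test, 49 gives 0.7996, so 50 are needed. One-sided: 39.
- With n = 30 and SD = 140, the difference detectable at 0.80 is **103 mm²**.
- With n = 30 and Δ = 80, the SD would have to be about **109 mm²** or less.

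**3. The planned three-group ANOVA, 30 per group, largest gap 80 mm².** The noncentrality is λ = n × Σ(mean − grand mean)²/SD².
- Means 0, 40, 80: λ = 30 × 3200/19600 = 4.90, power 0.48.
- Means 0, 0, 80: λ = 30 × 4267/19600 = 6.53, power 0.61.

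**4. The pairs at other group sizes** (t test, two-sided, SD 140). The second row for each pair assumes the 4.3 % dropout reported so far in the Discussion: 35 × 0.957 = 33.5 and 50 × 0.957 = 47.9, taken as 33 and 48. These are not final numbers, since the protocol allows inclusions to be adjusted.

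| Pair | n | Power for 80 mm² | Detectable at 0.80 |
|---|---|---|---|
| HRTW vs LITW | 35 vs 35 (no dropout) | 0.65 | 95 mm² |
| HRTW vs LITW | 33 vs 33 | 0.63 | 98 mm² |
| WHEY vs HRTW or LITW; WHEY or COLL vs CARB | 50 vs 35 (no dropout) | 0.73 | 87 mm² |
| WHEY vs HRTW or LITW; WHEY or COLL vs CARB | 48 vs 33 | 0.70 | 90 mm² |
| WHEY vs COLL | 50 vs 50 (no dropout) | 0.81 | 79 mm² |
| WHEY vs COLL | 48 vs 48 | 0.79 | 81 mm² |

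Only WHEY vs COLL comes to 0.80, and strictly only if nobody drops out.

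**5. Readings that would give more than 0.80 at n = 30.**
- One-sample or paired test with SD 140: 0.571 × √30 = 3.13, power 0.856 (27 subjects suffice).
- 140 read as the SD of a difference between two individuals: per-group SD = 140/√2 = 99, power 0.868 (26 per group).

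**6. Side check on the percentages.** 300/0.065 = 4615 mm², while 80/0.02 = 4000 mm². Two per cent of 4615 is 92.3 mm², which has power 0.709 at 30 per group. The choice of base does not rescue the claim.

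**The case against.** The best defence is that the SD is loosely worded. It is attached to an expected change between intervention groups, so it might be meant as the SD of a between-person difference; the per-group SD would then be 99 mm² and the power 0.868. The source of the figure is a cited study that is not available here. This reading cannot be ruled out, but the text does not state it. The ordinary meaning is the between-participant SD of the change, and no other SD is offered. If the authors meant something else, the paragraph needs correcting anyway.

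A second defence is that the expected difference is 300 mm², for which 30 per group has power above 0.999. That is true and limits the consequence: the trial is not underpowered for the effect its authors expect. But the protocol sets its goal at about 2 % and ties the group size to 80 mm², so the statement about 80 mm² must be right in its own terms.

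It is also fair to say that the document nowhere announces that it will read a null result as excluding 2 %; that is a foreseeable use, not a stated plan. And the mismatch between the percentages is minor, since the text calls its figures approximate: 80/4615 is 1.7 %, which rounds to 2 %.

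That a one-sample formula was applied to a between-group question is a plausible explanation of the figure, but only an inference. The finding does not depend on it.

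**Conclusion.** The power statement for the primary outcome is wrong as written. With the stated SD, alpha and group size, power to detect 80 mm² between two groups is 0.59 two-sided (0.71 one-sided), and 0.48 to 0.61 for the planned three-group F test. The difference detectable at 0.80 with 30 per group is 103 mm²: 2.2 % if the mean CSA is 4615 mm², or 2.6 % if it is 4000 mm². No between-group calculation that takes 140 mm² as the SD of the change in each group reaches 0.80.

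This rests on three assumptions: 140 mm² is the between-participant SD of the 12-month change, the analysis is unadjusted as described, and the pairwise test is two-sided. The shortfall concerns the 80 mm² goal only; the 300 mm² expectation is unaffected.

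**What to change.** - Replace the claim with figures that follow from the inputs: with 30 completers per group and SD 140 mm², power is 0.80 for about 103 mm² and 0.59 for 80 mm².
- If the original figure used a different SD, a different meaning of 140 mm² or another formula, state it and show that it fits a between-group comparison.
- Give the detectable difference for each planned pair at the actual numbers of completers, since the groups differ in size.
- Use one base for converting mm² to per cent.
- State that a non-significant comparison will not be taken to exclude an 80 mm² (2 %) difference, and report confidence intervals for the differences. This matters most for HRTW against LITW.

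The cost is a change of wording here and wherever else the power claim is repeated. The stated precision becomes less favourable; no participants are added.

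### The muscle protein synthesis sub-study is sized on an absolute change in %/h, but the only between-group test is an ANOVA of relative changes, which breaks down if applied per participant to responsiveness

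*Protocol article*

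**What the plan says.** All of this is in the protocol article, under Statistics and power calculations. Three quantities appear for one endpoint.

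- **Outcome, within a visit.** "the outcome measure is the relative change in the FSR of muscle proteins from the basal condition", running from the fasted resting state to the 4-hour postprandial average. The denominator is basal FSR.
- **Sizing, in absolute units and within group.** The starting value is an "expected average 4-h postprandial responsiveness to protein feeding from basal condition of 0.016 %/h", described as roughly a 50% rise in FSR, "with an interparticipant SD on the increase of 0.017 %/h". The target is stated as "We aim to be able to detect a 50 % change in responsiveness within a group over the course of the 12-month period", spelled out as 0.008 %/h (0.016 to 0.024). "The SD for the change in responsiveness is set as 0.006 %/h". The claim is: "By including 10–12 participants, we obtain a power of at least 0.80 to detect a statistical difference over time within each intervention group".
- **Test, between groups.** The closing paragraph of the section prescribes "one-way analysis of variance of the relative group changes from baseline to 12 months" for two three-group comparisons. It is written for the trial's data in general. It makes no exception for MPS, and no other between-group test is given.

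**The concern.** The scale that was powered is not the scale of the named outcome, nor that of the prescribed test. The mismatch with the test has consequences. A relative change from baseline to 12 months needs a baseline safely above zero. Quadriceps area meets that condition. MPS responsiveness does not: it is a difference between two rates, and by the protocol's own figures its SD (0.017) exceeds its mean (0.016).

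Some participants will therefore start with a response at or below zero. For them a genuine improvement, divided by a negative baseline, is recorded as a decline. Others start just above zero, and an ordinary improvement becomes several hundred percent. A few such values dominate an arm of 12 to 15.

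The sub-study exists to link differences in muscle gain to changes in the anabolic response to protein. On the prescribed scale it could miss the improvement it was sized to detect, or show it with the wrong sign.

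**Working it through.** **Inputs**, all from Statistics and power calculations: baseline responsiveness mean 0.016 and SD 0.017 %/h; 12-month change 0.008 %/h with SD 0.006 %/h; 10 to 12 analysed per group; alpha 0.05, taken as two-sided because sidedness is not stated. Enrolment is 3 × 12 + 2 × 15 = 66.

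**1. The stated power reproduces on the absolute scale.** For a paired t-test, the standardised change is 0.008/0.006 = 1.333. The noncentral t distribution gives:

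| n per group | Power, absolute change |
|---|---|
| 7 | 0.83 |
| 10 | 0.96 |
| 12 | 0.99 |

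The claim of at least 0.80 is met with room to spare. The 50% in the target is a ratio of group means (0.008/0.016), not an average of individual percentages.

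**2. Share of baselines at or below zero.** Under normality, Φ(−0.016/0.017) = Φ(−0.941) = 0.173. The expected counts are 12 × 0.173 = 2.1, 15 × 0.173 = 2.6 and 66 × 0.173 = 11.4. The chance of at least one in an arm of 12 is 1 − (1 − 0.173)^12 = 0.90. A heavier-tailed shape (t on 5 df, same SD) gives 13.9%. A further difficulty is that about 12% of baselines lie within ±0.004 %/h, where the percentage is very large in either direction.

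**3. What the percentage does to the same true gain of 0.008 %/h.**

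| Baseline | 12 months | Absolute change | Relative change |
|---|---|---|---|
| 0.016 | 0.024 | +0.008 | 0.008/0.016 = +50% |
| 0.002 | 0.010 | +0.008 | 0.008/0.002 = +400% |
| −0.005 | 0.003 | +0.008 | 0.008/(−0.005) = −160% |

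**4. Power if the relative change is formed per participant.** This was simulated with 40,000 groups of 12, using a normal baseline, the protocol's mean change and SD, and a within-group t-test. Two assumptions about how change relates to baseline were tried, because the documents do not settle it. Under the second, the correlation between visits is 1 − 0.006²/(2 × 0.017²) = 0.938.

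| Assumption | Power, absolute | Power, percent | Group mean percent below zero |
|---|---|---|---|
| Change independent of baseline | 0.99 | 0.15 | 28% |
| Equal SD at both visits | 0.99 | 0.13 | 30% |

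The true change is +50% of the group mean in every case. About 16% of participants have a real gain recorded as a negative percentage.

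**5. Does the within-visit ratio escape this?** Basal FSR implied by the protocol is 0.016/0.5 = 0.032 %/h. Its SD is not given. Assuming 0.005 to 0.012 %/h, the chance of a basal value at or below zero is at most 0.4%, so the ratio within one visit is well behaved. But the baseline ratio has the sign of the baseline increment. If that ratio is then expressed as a relative change over 12 months, the same 17% of denominators are at or below zero.

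**The case against.** The strongest reply is that the outcome sentence is sound. Its denominator is basal FSR, which is positive. A participant with no response scores zero, and one with a negative response scores below zero; both are defined and correctly signed. This stands. A reader might infer from the 17% that the outcome as defined is undefined or reversed for those participants. The documents do not support that, because the 17% describes the increment, which is the numerator of that ratio.

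A second reply is that the ANOVA sentence is general, does not mention MPS, and might mean a ratio of group means, while the comparison powered for MPS is within group and in %/h. This stands in part and makes the point conditional. Still, a one-way ANOVA needs a value per participant, the sentence makes no exception for MPS, and no other between-group test is offered. Detail can be left to an analysis plan, but here the article itself states an outcome, a sizing and a test that do not match.

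Third, whether anabolic sensitivity is a proportional or an absolute response is a choice of estimand. That is fair, and preferring the proportional form is not an error in itself. Two related arguments are not relied on. That a rise in basal FSR would hide a real gain depends on a rise the documents do not give. Which precursor pool leads the FSR calculation is detail the full protocol or analysis plan may settle.

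**Conclusion.** The point holds in conditional form. If the general relative-change ANOVA is applied per participant to MPS responsiveness, about 17% of baseline denominators are at or below zero. Within-group power at n = 12 then drops from 0.99 to about 0.15 (0.13 to 0.15 across the two assumptions), and the group mean takes the wrong sign in 28 to 30% of groups. The 17% assumes normality; the power figures also take the protocol's SD of change at face value.

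A reader might go further and conclude that the stated power is wrong or that the endpoint cannot be interpreted. Neither follows. The power claim is correct for the absolute within-group change, and the within-visit ratio is interpretable. What is missing is agreement between the sized quantity and the tested one: the 0.80 refers neither to the ratio named as outcome nor to the between-group ANOVA.

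The consequence is confined to a secondary outcome in a subset of 66. The primary outcome, quadriceps cross-sectional area, is not affected. The change should be made, but the trial's main conclusion does not depend on it.

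**What to change.** In Statistics and power calculations:

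- Define MPS responsiveness as postprandial minus basal FSR, in %/h.
- Make the 12-month outcome its absolute change from 0 to 12 months, analysed within each group (the comparison already powered) and between groups in the two planned three-group comparisons.
- State that this outcome is exempt from the relative-change ANOVA rule.
- Report the response as a percentage of basal FSR, at each visit, as supportive.
- Say that the stated power applies to the within-group absolute change.

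The cost is wording only: no new participants, biopsies, samples or assays. The change should be fixed before the MPS data are analysed.
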